# Efficacy and safety of pembrolizumab as first-line treatment for advanced non-small cell lung cancer complicated with chronic obstructive pulmonary disease: protocol for a prospective, single-arm, single-center, phase II clinical trial

**DOI:** 10.3389/fonc.2024.1179232

**Published:** 2024-03-07

**Keywords:** chronic obstructive pulmonary disease, pembrolizumab, efficacy, safety, non-small cell lung cancer (NSCLC)

## Abstract

**Background:**

The first-line standard treatment option for patients with NSCLC complicated with Chronic obstructive pulmonary disease (COPD) is still unclear and relies on the treatment option of NSCLC alone. To date, a limited number of retrospective studies have explored the efficacy and safety of immunotherapy in patients with NSCLC complicated with COPD. We therefore designed this study to further explore the efficacy and safety of first-line immunotherapy in patients with NSCLC complicated with COPD.

**Methods:**

This study was designed as a single-armed, single-center, prospective, phase II clinical study. It will include 30 advanced (stage IV) NSCLC combined with COPD primary treatment subjects. Each subject’s diagnosis will be confirmed by clinical, radiographic, pathologic, and pulmonary function evaluation. A fixed dose of 200 mg pembrolizumab will be administered by intravenous infusion on day1 every 3 weeks (Q3W). The management of stable and acute exacerbations of COPD include home oxygen therapy, and the use of conventional medications are also administered. Imaging evaluation will be performed every 6 weeks for 6 months from the first pembrolizumab dose and approximately every 12 weeks thereafter until disease progression or early withdrawal. COPD status will be evaluated every 3 months by pulmonary function, GOLD grading, mMRC score, CAT score, ABCD grouping, and AECOPD severity. The primary outcome is Progression-free survival. The secondary outcome measures include objective response rate, overall survival, rate of acute exacerbations of COPD (times/year), lung function, mMRC score, CAT score, impact of treatment on patient’s health-related quality of life, antibiotic use (including duration and classes), and adverse events associated with immune checkpoint inhibitors. Exploratory endpoint is to explore the association between COPD grade and the degree of immune cell (CD4+ T lymphocytes and CD8+ T lymphocytes) infiltration, as well as the association between COPD grade and the efficacy of immune checkpoint inhibitors.

**Clinical trial registration:**

ClinicalTrials.gov, identifier NCT05578222.

## Introduction

Chronic obstructive pulmonary disease (COPD) is the third leading cause of death, and lung cancer is the second most common type of cancer worldwide. Both have high global incidence and mortality rates, which significantly increase socioeconomic burden (1–3). Smoke exposure, family history (genetic predisposition), and chronic inflammation are common risk factors for COPD and lung cancer (4), with smoking being the leading risk factor for lung cancer and COPD. COPD is associated with an increased lung cancer development, which is often underestimated in clinical practice. Studies have reported that 40-70% of lung cancer cases are complicated with COPD (5, 6).

COPD affects the incidence of lung cancer and may also influence the efficacy of cancer therapies (7, 8). An abnormal inflammatory response plays a role in the occurrence and development of both diseases. The tumor microenvironment of lung cancer is conducive to angiogenesis and immunosuppression, which eventually leads to the immune escape of tumor cells and tumor formation (9, 10). COPD-like chronic inflammation is associated with immune escape mediated by the programmed death-1 (PD-1)/programmed cell death 1 ligand 1 (PD-L1) pathway and has been shown to be involved in the occurrence and development of COPD-associated lung cancer (10). In addition, in a COPD mouse model complicated with lung cancer, chronic inflammation negatively affected the efficacy of immune checkpoint inhibitors (10, 11).

Pembrolizumab is a humanized monoclonal antibody against PD-1 used in cancer therapy. To date, five randomized clinical trials have demonstrated the substantial efficacy of pembrolizumab in non-small cell lung cancer (NSCLC). The Phase III KEYNOTE-024 trial showed that first-line pembrolizumab monotherapy improved progression-free survival (PFS, 10.3 vs. 6.0 months, hazard rate [HR] = 0.50) and overall survival (OS; 30.0 vs. 14.2 months, HR = 0.63) when compared with chemotherapy. In addition, pembrolizumab treatment resulted in fewer adverse events (AEs) among patients with metastatic NSCLC without EGFR/ALK alterations and a PD-L1 tumor proportion score of 50% or greater (12). KEYNOTE-042 expanded the inclusion criterion to PD-L1 tumor cell proportion score (TPS) ≥ 1%, and the results suggested that pembrolizumab significantly reduced the risk of death by 19% compared with chemotherapy. However, subgroup analysis suggested that the main beneficiary group was patients with PD-L1 TPS ≥ 50% (13). The results of thesubgroup analysis showed that compared with chemotherapy, pembrolizumab significantly prolonged the OS of patients with PD-L1 TPS ≥ 50% (median 20.0 vs. 14.0 months, HR = 0.62) and those with PD-L1 TPS 1–49% (median 19.9 vs. 10.7 months, HR = 0.69) (14). In 2019, the National Medical Products Administration approved pembrolizumab as the first-line treatment for patients with PD-L1 TPS ≥ 1%. According to the Chinese Society of Clinical Oncology guidelines, pembrolizumab is recommended for the first-line treatment of advanced driver negative NSCLC (Grade I recommendation), with PD-L1 TPS ≥ 50% as class 1A evidence and PD-L1 TPS ≥ 1% as class 2A evidence.

However, the KEYNOTE series of NSCLC-related studies did not consider COPD comorbidities. COPD patients often have a history of smoking. El-Osta et al. (15) found that smoking has been linked to increasing the immunogenicity of tumor cells and may improve the efficacy of immunotherapy. In addition, Malek AE et al. (16) have shown that COPD and smoking are independently associated with an increased risk of infection in patients treated with immune checkpoint inhibitors. Therefore, the efficacy and safety of pembrolizumab as a first-line treatment of patients with advanced NSCLC complicated with COPD are unclear. Retrospective studies have shown that the efficacy of PD-1/PD-Ll immune checkpoint inhibitors in patients with COPD combined with lung cancer is better than that in patients with lung cancer alone (17–19). However, these studies have some limitations. First, known clinical data were obtained retrospectively, and there are many confounding factors that may affect the results, such as age, pathological type of NSCLC, COPD grade, smoking status, and hormone use. Second, the influence of COPD on immune cell infiltration in tumor tissue is unclear. A study by Biton (17) showed that tumor-specific CD8+ T cell depletion positively correlated with COPD severity. However, Mark et al. (18, 20, 21) found that the infiltration level of tumor-specific CD4+ and CD8+ T cells in patients with COPD complicated with lung cancer was higher than that of patients without COPD. In addition, findings regarding the correlation between COPD and PD-L1 expression in NSCLC tissues are conflicting. Third, previous studies have suggested that PD-1/PD-Ll immune checkpoint inhibitors could aggravate lung tissue damage and COPD symptoms (19, 22). However, these studies lacked parameters, such as the GOLD scale, mMRC dyspnea questionnaire, CAT score, and ABCD grouping, which limited COPD assessment. Therefore, in this clinical trial, we aim to evaluate the efficacy and safety of pembrolizumab as a first-line treatment for advanced NSCLC with COPD.

## Methods

### Study design

This study was designed as a single-arm, single-center, prospective, phase II clinical study. It will include 30 advanced (stage IV) NSCLC combined with COPD primary treatment subjects. The diagnosis of each subject will be confirmed by clinical, radiographic, pathologic, and pulmonary function evaluation. Patient recruitment was initiated in November 2022, and we plan to complete the study in December 2024. This trial has been approved by the Institutional Review Board of Tian Chest Hospital (Approval date: August 25, 2022 and approval number: 2022KY-012-01) and has been registered in the clinicaltrials.gov database (NCT05578222). A schematic diagram of the trial is presented in **Figure 1**.

**Figure 1 f1:**
[figure not shown]
A schematic diagram of subjects’ enrolment, interventions, assessments, and visits.

### Eligibility criteria

Adult patients with treatment-naïve, confirmed advanced (stage IV) NSCLC combined with COPD, PD-L1 TPS ≥ 1%, and an Eastern Cooperative Oncology Group performance status of 0 to 2 will be enrolled. As mentioned previously, NSCLC stage and diagnosis will be confirmed by clinical, radiographic, pathologic, and pulmonary function evaluation. Inclusion and exclusion criteria are shown in **Table 1**.

**Table 1 T1:** Inclusion and exclusion criteria.

Key inclusion criteria
Ø Signed written informed consent before enrollment; Ø Men and women aged 18-75; Ø The patient must be able to provide fresh or archived tumor tissue and its pathology report; Ø No previous antitumor therapy, life expectancy is not less than 12 weeks; Ø Newly diagnosed NSCLC subjects confirmed by pathology and imaging, Stage: cT1-4N1-3M1 (stage IV), AJCC eighth edition clinical staging of lung cancer; Ø Asymptomatic patients with NSCLC brain metastases; Ø PD-L1 tumor fraction (TPS) ≥1%; Ø Epidermal growth factor receptor (EGFR) gene mutation negative and anaplastic lymphoma kinase (ALK) negative; Ø Measurable lesions that meet RECIST v1.1 Criteria; Ø Patients with COPD who met the relevant diagnostic criteria for COPD in the Guidelines for the Diagnosis and Treatment of Chronic Obstructive Pulmonary Disease (Revised 2021) formulated by Chinese Society of Respiratory Medicine, and whose condition was stable for ≥2 weeks; Ø ECOG: 0 ~ 2; Ø The functions of vital organs meet the following requirements (excluding the use of any blood components and cell growth factors within 14 days): Normal bone marrow reserve, neutrophil (ANC) ≥1,500/mm³, platelet count (PLT) ≥100,000/mm³, hemoglobin (Hb) ≥5.6mmol/L (9g/dL); Creatinine (Cr) ≤1.5 mg/d and/or Clearance of creatinine (CCr) ≥60 ml/min; Normal liver function or Total Bilirubin (TBIL) ≤1.5ULN, Aspartate Transaminase (AST) and Alanine Transaminase (ALT) ≤1.5 ULN; Ø Non-surgical sterilization or use of a medically approved contraceptive method (e.g. intrauterine device, birth control pill, or condom) during the study treatment period and for 3 months after the end of the study treatment period. Patients with non-surgical sterilization or women of childbearing age had to have a negative serum or urine HCG test within 7 days before study enrollment; Must be non-lactation period; Male patients who are not surgically sterilized or of childbearing age are required to consent to use a medically approved contraceptive method with their spouse during the study treatment period and for 3 months after the study treatment period; Ø Subjects volunteered to join this study, with good compliance, safety and survival follow-up.
Key exclusion Criteria
Ø Previous radiotherapy, chemotherapy, long-term or high-dose hormone therapy, surgery, or molecular targeted therapy; Ø The subject has previous or concurrent other malignant tumors; Ø History of asthma or other respiratory diseases (bronchiectasis, tuberculosis, interstitial pneumonia, occupational lung disease, sarcoidosis, etc.); Patients with objective evidence of radiation pneumonitis, drug-associated pneumonitis, or severe impairment of pulmonary function; Ø History of lobectomy; Ø A history of clinically significant circulatory failure; Ø Significant contraindications for spirometry (history of myocardial infarction, cerebral artery or aortic aneurysm, history of eye surgery, hemoptysis); Ø Patients with rheumatic diseases; Patients with heart, cerebrovascular, liver, kidney, hematopoietic system and other serious primary diseases; Ø Patients with a history of acute gastrointestinal bleeding within 3 months; Ø Previous immune checkpoint inhibitor therapy; The subject is known to have a previous allergy to macromolecular protein preparations, or to any PD-1 mab component; Ø The subject has any active autoimmune disease or a history of autoimmune disease (e.g., not limited to autoimmune hepatitis, interstitial pneumonia, uveitis, enteritis, hepatitis, hypophysitis, vasculitis, nephritis, hyperthyroidism, hypothyroidism; Subjects with vitiligo or complete remission of asthma in childhood without any intervention as adults were included; Subjects with asthma requiring medical intervention with bronchodilators were excluded); Ø The subject has active infection or unexplained fever >38.5 ℃ during the screening period or before the first administration; Ø Subjects with innate or acquired immune deficiency, such as HIV infection, or active hepatitis (transaminases did not meet the inclusion criteria, HBV DNA≥10^4^/ml, HCV RNA≥10³/ml); Chronic hepatitis B virus carriers, HBV DNA≥2000 IU/ml (≥10^4^copies/ml), must receive antiviral therapy during the trial to be enrolled; Ø The subject is participating in another clinical study or it has been less than one month since the end of the previous clinical study; Subjects may receive other systemic antitumor therapy during the study; Ø Receive live vaccine less than 4 weeks before or during the study period possibly; Ø The subject cannot or does not agree to pay for the examination and treatment expenses at his own expense; Ø Pregnant or lactating women; Ø Other conditions that should be excluded from the study in the opinion of the investigator

### Patient withdrawal

Patients will be withdrawn from this study for the following reasons: (1) Subject or legal representative requests early withdrawal; (2) Unexpected rapid progression or radiographically confirmed disease progression occurs; (3) COPD-related exacerbations progress to acute exacerbation of chronic obstructive pulmonary disease (AECOPD) grade II-III; (4) Occurrence of any of the following during treatment: grade 3 hematologic toxicity, grade 3 neutrophil count decrease with fever (>38.5°C), grade 3 thrombocytopenia with bleeding tendency, esophageal perforation, severe pulmonary/mediastinal infection, hemorrhage, myocardial infarction, heart failure, severe arrhythmia, grade 2 or higher grade immune pneumonia, grade 3 or higher grade immune hepatitis, infusion reactions, or other immune-related toxicity; (5) 2-week treatment delay (for any reason); (6) Pregnancy; (7) The investigator considers it necessary to withdraw a patient from the study; (8) Subject cannot be followed up. All patients who withdraw will be followed up according to the study protocol, and the follow-up results will be recorded unless the patient withdraws informed consent and refuses to follow-up.

### Study treatments

The management of stable and acute exacerbations of COPD include home oxygen therapy and the use of conventional medications such as bronchodilators, inhaled corticosteroids, and expectorants.

A fixed dose of 200 mg pembrolizumab will be administered via intravenous infusion on day 1 every 3 weeks (Q3W). The efficacy will be evaluated according to the Response Evaluation Criteria in Solid Tumours (RECIST) v1.1 evaluation criteria. If a progressive disease (PD) result is obtained, medication use will be continued in patients with clinically stable symptoms and in patients that could potentially benefit from continued treatment. Efficacy will then be re-evaluated after 4 weeks using the immune-related response criteria (irRC) criteria. If the reassessment result is no progression, treatment will be continued. Treatment will also be continued (with consent) if the result is progression, the subject has no other treatment options, or the investigator believes that the patient would benefit from continued treatment. Patients will be withdrawn from the study upon their or the investigator’s request or owing to PD or intolerable toxicity.

Drugs that interfere with hepatic P450 enzymes and cause QT prolongation in the heart, traditional Chinese medicines, and immunological agents with anticancer properties will be contraindicated or used with caution during the study period. At the end of the treatment period, the investigator will recommend follow-up treatment.

### Outcome measurements

The primary outcome is PFS, defined as the time from randomization initiation to the progression of tumor or death for any reason (refer to RECIST v1.1).

The secondary outcomes include objective response rate (ORR), overall survival (OS), rate of acute COPD exacerbations (times/year), lung function, mMRC score, CAT score, impact of treatment on patient’s health-related quality of life (HRQoL), antibiotic use (including duration and classes), and AEs associated with immune checkpoint inhibitors. ORR is defined as the proportion of patients with complete response (CR) and partial response (PR) and is used to estimate the treatment efficacy according to RECIST v1.1. OS was measured as the period from the diagnosis of lung cancer to death. Acute exacerbation was defined if respiratory tract symptoms such as cough, sputum production, and dyspnea were significantly worse than usual, and the treatment program had to be adjusted, such as by using oral or intravenous glucocorticoid treatment combined with or without antibiotics, while excluding pneumothorax, heart failure, pneumonia, and other diseases. Acute exacerbations of COPD are classified as Grades I-III according to clinical symptoms.

Exploratory endpoint is to explore the association between COPD grade and the degree of immune cell (CD4+ T lymphocytes and CD8+ T lymphocytes) infiltration, as well as the association between COPD grade and the efficacy of immune checkpoint inhibitors.

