### Study schedule and assessments

The study flow and visit schedule are shown in **Table 2**. Baseline data, such as ECOG score, QLQ-C30 score, height, weight, physical examination, vital signs, laboratory examination, electrocardiogram, lung function, mMRC score, CAT score, ABCD grouping, and AECOPD severity, will be recorded during the screening period (less than 2 weeks prior to initial administration of the study drug). Previous and recent tumor samples will be collected. The expression of PD-L1 in tumor tissue samples will be determined via immunohistochemical staining, and the expression of CD4+ and CD8+ T lymphocytes will be determined via immunofluorescence staining.

**Table 2 T2:** Study flow chart and visit schedule.

FLOW CHART	Screening	Treatment visit	End of treatment visit	Safety follow-up visit
Timepoint	-d14–d0	Before dosing every cycle	Within 7 days after termination of treatment	Within 30 days after the last dose
Informed consent	X			
Inclusion and Exclusion criteria	X			
Demographic characteristics	X			
Medical history and treatment history	X			
Physical examination	X	X	X	X
ECOG score	X	X	X	X
QLQ-C30 score	X	X	X	X
Vital sign	X	X	X	X
Tumor tissue sample	X			
Virus detection:HbsAg,HbsAb,HbcAb,HCVAb,HIVAb	X			
Complete blood count, Urine Routine Examination	X	X	X	X
Alanine aminotransferase, Aspartate aminotransferase, Direct bilirubin, Total bilirubin, Glucose, Potassium,Sodium,Calcium, Phosphorus, blood urea nitrogen,Creatinine,Creatinine clearance, Total cholesterol	X	X	X	X
Activeated partial thromboplastin time, Prothrombin time, Thrombin time,International Normalized Ratio	X	X	X	X
Pregnacy test	X		X	
Free triiodothyronine, Free thyroxine, Thyroid-stimulating hormone	X	X	X	X
Cortisol, Adrenocorticotropic hormone	X	X	X	X
12-lead electrocardiogram	X	X	X	X
Echocardiography	X			
Lung function	X	Once every 3 months	X	
Evaluation of COPD symptoms	X	Once every 3 months	X	
Risk assessment of COPD exacerbations	X	Once every 3 months	X	
Evaluation of severity of acute exacerbation of COPD	X	Once every 3 months	X	
Drug administration		X		
Chest and abdominal CT (or abdominal and adrenal ultrasound), Cranial enhanced MRI,Neck ultrasound, Bone ECT, PET-CT	X	X		
Adverse events and drug combinations	X	X		
Survival follow-up		X		

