Baseline tumor imaging evaluation will be completed within 2 weeks of initial treatment. Imaging evaluation will be performed every 6 weeks for 6 months from the first pembrolizumab dose and approximately every 12 weeks thereafter until disease progression or early withdrawal. The anti-tumor efficacy will be evaluated according to RECISTv1.1 and irRC (23).

Pembrolizumab-related AEs will be determined after each treatment cycle. The severity of AEs will be determined according to NCI-CTC AE 5.0. Investigators will be responsible for the appropriate measurement of AEs and will determine the relationships between AEs and the study drugs. AEs will be followed up until they were grades 0 to 1 or stabilized or returned to baseline levels. COPD status will be evaluated every 3 months according to pulmonary function, GOLD grading, mMRC score, CAT score, ABCD grouping, and AECOPD severity (24).

HRQoL will be assessed by completing the European Organisation for Research and Treatment of Cancer core quality of life questionnaire (QLQ-C30) at baseline, evaluation visits, end-of-treatment visits, and safety follow-up visits (within 30 d after the last dose).

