### Data management

A paper case report form (CRF) will be developed before commencing the study. Patient information will be recorded using the CRF. The data manager will verify the CRF data, which will then be entered into a data management system. Doubtful data will be provided to the researchers for verification. Patient-identifying information, such as name, telephone number, and home address, will not be entered into the data management system. The verified data will be sent to statisticians for statistical analysis.

Some useful measures are often used to minimize the occurrence of lost follow-up. Firstly, a clinical nurse will be arranged to maintain long-term contact with the patien, and save information on commonly used contact methods of the patient such as telephone number, WeChat, email address, among others. In addition, the nurse will be in contact with the patient every other day to monitor the patient for immune-related adverse reactions. When the patient reports an adverse reaction, the nurse will promptly report it to the doctor, who will then contact the patient and give reasonable treatment. At the same time, it is also very important to save the contact information of at least one family member of the patient, so that the patient can be contacted in a timely manner.

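### The only listed adverse-event outcome covers checkpoint-inhibitor-associated events, so a non-fatal, non-exacerbation infection judged unrelated to the drug is directly counted by no listed outcome

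*Protocol article*

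**What the plan says.** The protocol article names one adverse-event (AE) outcome. In Outcome measurements the list of secondary outcomes closes with "antibiotic use (including duration and classes), and AEs associated with immune checkpoint inhibitors". The abstract's Methods paragraph has the same restriction: "adverse events associated with immune checkpoint inhibitors".

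Study schedule and assessments opens its AE paragraph in the same vein: "Pembrolizumab-related AEs will be determined after each treatment cycle". It then has events graded by CTCAE version 5.0, says that investigators "will determine the relationships between AEs and the study drugs", and follows events until they resolve or stabilise. The corresponding row of Table 2, "Adverse events and drug combinations", carries no causality limit. Planned analyses assigns the safety data to the safety set, also without a limit.

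Three other statements bear on infection:

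- The Introduction reports that "COPD and smoking are independently associated with an increased risk of infection in patients treated with immune checkpoint inhibitors" and draws on this when it concludes that efficacy and safety in these patients are unclear.
- The definition of an acute COPD exacerbation in Outcome measurements rules out pneumonia, along with some other diagnoses.
- Patient withdrawal lists "severe pulmonary/mediastinal infection" among the reasons for leaving the study, with follow-up continuing unless consent is withdrawn.

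**The concern.** The trial sets out to describe safety in patients with both lung cancer and COPD, and infection is a risk that its own rationale raises. With pneumonia properly kept out of the exacerbation rate, the AE outcome is the only place left where a non-fatal pneumonia could be counted as an event. As worded, that outcome admits the case only if the investigator links it to the drug.

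Attribution is hard in this setting, because COPD is a ready alternative explanation for a chest infection. A randomised trial would have a control rate to show whether too many events had been put down to the underlying disease. This single-arm, single-centre trial has none. The reported safety result would then depend partly on individual causality judgements, for a type of event that the rationale singles out.

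**Working it through.** No arithmetic applies, since the article gives no figure on this point. The check is to take each listed outcome and ask whether it counts a given infection as an event. Outcome measurements lists one primary outcome, nine secondary outcomes and two exploratory associations.

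**Infections that are counted**

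- A fatal infection is a death from any cause, so it enters progression-free survival and overall survival.
- An infective episode that meets the exacerbation definition enters the exacerbation rate.
- An infection judged related to the drug enters the AE outcome.

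**A non-fatal pneumonia judged unrelated**

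- Progression-free survival, overall survival and objective response: not counted, as there is no death and the pneumonia is not a tumour assessment.
- Exacerbation rate: not counted, because the definition excludes pneumonia.
- Lung function, mMRC, CAT and quality of life: the scores may shift, but none of them counts the event.
- Antibiotic use: a treated case contributes, and no attribution is needed. However, the outcome is listed by duration and class, not by indication. The exacerbation definition also allows antibiotics as treatment, so the outcome cannot tell a pneumonia from an exacerbation.
- AEs associated with checkpoint inhibitors: not counted once the event is judged unrelated.
- Exploratory associations of COPD grade with T-cell infiltration and with efficacy: not relevant to the event.

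No listed outcome counts the event directly. The same holds for any other non-fatal infection that is not an exacerbation and is judged unrelated.

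**Is the restrictive reading the right one?** The wording in Outcome measurements could be taken loosely, as any event that occurs on treatment. Two statements in Study schedule and assessments point the other way: the opening sentence speaks of pembrolizumab-related events, and the investigator has to decide on causality. Even if the loose reading were intended, the text would need rewording to say so.

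**The case against.** The strongest reply is that the data are almost certainly there. Table 2 and most of the AE paragraph set no causality limit, relatedness can be judged only if unrelated events are also recorded, and the safety analysis is unrestricted. Tables of all-cause events are also what a full protocol or analysis plan usually specifies, and neither is shown. Infection is partly visible through antibiotic use, and severe cases through withdrawal.

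Most of this stands, and it makes the point small. It does not remove it. The article does more than leave a detail to another document: it states the outcome, in two places, with a limit. Recording an event does not make it part of a defined outcome, and antibiotic use does not identify the infection.

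Three stronger readings are tempting, and the documents do not support them.

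- *Unrelated events are not collected or looked for.* A reader might infer this from the opening AE sentence, or from Data management, where "the nurse will be in contact with the patient every other day to monitor the patient for immune-related adverse reactions". The unrestricted statements above speak against it. The next sentence in Data management has the nurse pass on any adverse reaction that the patient reports, without limiting it to immune-related ones.
- *AE recording stops before the end-of-treatment and safety follow-up visits.* In the Table 2 text at hand, the AE row is marked only at screening and treatment visits. The survival follow-up row below it is marked only at treatment visits, which makes little sense for overall survival and suggests that merged cells were lost. Assessment after each three-week cycle would in any case cover 21 days after the last dose. No finding rests on this.
- *A particular number of the 30 patients will be missed.* The article gives no infection risk and no share judged unrelated, so any such number would only restate the assumptions behind it.

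**Conclusion.** The point holds in a narrow form. The listed AE outcome is limited by attribution, and a non-fatal, non-exacerbation infection judged unrelated to pembrolizumab is directly counted by no listed outcome. In an uncontrolled trial whose rationale cites infection risk, this makes the safety result depend on causality judgements that nothing in the design can check.

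The size cannot be determined from the document. The conclusion rests on reading the AE outcome as restrictive, which Study schedule and assessments supports, and on the outcome list in the article being complete. It does not touch the primary analysis, the sample size, eligibility or patient protection. It is a point about the scope of a secondary outcome and has minor priority.

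**What to change.** In Outcome measurements and in the abstract, define the safety outcome as all treatment-emergent AEs regardless of attribution, with onset from the first dose of pembrolizumab to the safety follow-up visit. Reword the opening AE sentence in Study schedule and assessments to match. On the safety set, report events by CTCAE v5.0 grade, show pneumonia and any infection separately, and give the drug-related subset alongside. Leave the exacerbation definition as it is, since excluding pneumonia there is right.

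The cost is wording changes in three places and one additional safety summary, with no new visit or test. The case report form is not shown, so whether its pages need changing is unknown. The safety report will be slightly longer and the overall AE figure less favourable. Without a control arm, the all-cause rate still cannot separate drug risk from background risk. The gain is a count that does not depend on attribution.

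### The primary PFS clock starts at a randomization that this single-arm trial does not have, and the OS clock starts at diagnosis, before patients can enter

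*Protocol article*

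**What the plan says.** All references are to the protocol article.

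- **Primary endpoint** (Outcome measurements): "The primary outcome is PFS, defined as the time from randomization initiation to the progression of tumor or death for any reason".
- **Overall survival, a secondary endpoint** (same section): "OS was measured as the period from the diagnosis of lung cancer to death".
- **Design** (Study design): "This study was designed as a single-arm, single-center, prospective, phase II clinical study". Table 2 lists consent, eligibility checks, dosing and follow-up, but no randomization step. Elsewhere the article uses the word randomized only for past or future trials.
- **Entry** (Eligibility criteria, Table 1): "Newly diagnosed NSCLC subjects confirmed by pathology and imaging" and "No previous antitumor therapy, life expectancy is not less than 12 weeks". PD-L1 TPS of at least 1% and negative EGFR and ALK results are also required. On tissue: "The patient must be able to provide fresh or archived tumor tissue and its pathology report".
- **Screening** (Table 2): day -14 to day 0, with consent in that column.
- **Imaging** (Study schedule and assessments): "Imaging evaluation will be performed every 6 weeks for 6 months from the first pembrolizumab dose".

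Nothing else in the article corrects either time origin.

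**The concern.** A time-to-event endpoint needs a start date that exists for every patient and does not come before the patient is at risk of being counted. Neither definition meets both conditions.

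The PFS start never occurs in this trial. Someone must choose a substitute, and if the choice is left until analysis it could be made with the data in view. Scans are counted from first dose, so any other origin also puts PFS on a different clock from its own assessments.

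The OS start is a real date, but too early for this use. A patient who dies, or becomes ineligible, between diagnosis and enrolment is never in the trial. Each patient who does enrol is credited with that interval as survival. This is left truncation (immortal time). If it is ignored, the error can only lengthen OS, and a single-arm trial has no control group in which it might cancel. PFS and OS would also start on different dates for the same patient.

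**Working it through.** The plan gives no figure for either time origin, so there is nothing to reproduce on this point. The sample size of 30 does not depend on it.

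**Inputs from the article.** Expected median PFS 6 months; enrolment 18 months and follow-up 12 months; 30 patients with 10% dropout (Determination of sample size). Screening window 14 days (Table 2). First scans every 6 weeks (Study schedule and assessments). Median OS on pembrolizumab 20.0 months for TPS of at least 50% (Introduction), used only as a scale.

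**Assumption.** The lag L from diagnosis to entry is not stated. I take 2 to 12 weeks. One month is 4.348 weeks.

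**1. OS.** For each patient, OS from diagnosis = OS from entry + L. With the same L for everyone, the median moves by exactly L.

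| Lag | L in months | L / 20.0 |
|---|---|---|
| 2 weeks | 2/4.348 = 0.46 | 2.3% |
| 4 weeks | 4/4.348 = 0.92 | 4.6% |
| 8 weeks | 8/4.348 = 1.84 | 9.2% |
| 12 weeks | 12/4.348 = 2.76 | 13.8% |

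If survival from entry is exponential with median 20 months, true 12-month OS is 0.5^(12/20) = 66.0%. Timed from diagnosis it reads 0.5^((12 - L)/20): 67.0% at L = 0.46 and 72.6% at L = 2.76.

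A lag that varies between patients gives much the same answer. In a simulation with a true median of 16 months and gamma-distributed lags averaging 1, 2 and 3 months, the median from diagnosis was 17.0, 18.0 and 19.1 months.

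**2. PFS.** Consent, enrolment and first dose should all lie within the screening window, so they differ by at most 14 days = 2/4.348 = 0.46 month. Against the expected median this is 0.46/6 = 7.7%. An earlier origin gives the longer PFS.

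**3. The PFS shift in proportion.** The 6-week scan interval is 6/4.348 = 1.38 months, about three times the largest shift. For sampling error, take exponential PFS with rate λ = ln 2/6 = 0.1155 per month and uniform accrual:

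P(event) = 1 - (e^(-12λ) - e^(-30λ))/(18λ) = 1 - (0.2500 - 0.03125)/2.079 = 0.895.

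With 30 × 0.9 = 27 evaluable patients this gives 27 × 0.895 = 24.2 events. An approximate 95% interval for a 6-month median is 6 × exp(±1.96/√24.2), or about 4.0 to 8.9 months. A shift of 0.46 month is small beside that width, but it is systematic.

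**The case against.** The strongest reply is that the PFS wording may simply be carried over from a randomized-trial template, that every sensible reading falls within two weeks, and that survival from diagnosis is a legitimate quantity whose delayed entry could be handled in an analysis plan not shown here. OS is also one of many secondary outcomes, with no hypothesis attached. Much of this stands. The PFS ambiguity is small, the OS bias is probably modest, and survival from diagnosis is valid when delayed entry is handled. What does not stand is leaving the text as it is. An article may omit detail, but these are stated definitions. One names an event that cannot occur, and the other suits a treatment-related reading only with an adjustment that the article does not mention.

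Three stronger readings are tempting, and the article does not support them.

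- A reader might add the COPD work-up and the two weeks of COPD stability to the guaranteed survival. Table 1 does not place either after the cancer diagnosis; COPD may already be known and stable, or be assessed in parallel.
- A reader might say that the trial's OS will be wrongly compared with the OS figures in the Introduction. No such comparison is planned. The design takes only its PFS expectation from the earlier pembrolizumab study.
- A reader might conclude that the OS result will be badly distorted. The lag is wholly assumed, and newly diagnosed, untreated patients point to a short one. Against that, the listed criteria set no maximum interval and allow archived tissue, so a longer lag is not excluded.

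**Conclusion.** The concern holds, at a limited size. The start of the primary endpoint is undefined as written. The practical range between readings is at most 14 days (0.46 month, 7.7% of 6 months), provided that the intended origin lies within the screening window. This is the part to settle first, because it concerns the primary endpoint and should not be left to be chosen once results are visible.

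OS from diagnosis is biased upward unless delayed entry is handled. The direction follows from the eligibility rules. The size, about 0.5 to 2.8 months or 2 to 14% of a 20-month median, rests on an assumed lag of 2 to 12 weeks and is likely to be toward the lower end. On its own, the OS point would be a modest matter for a secondary endpoint.

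**What to change.** Replace both origins with one stated date for PFS and OS, before any analysis.

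- The date of first pembrolizumab dose is the natural choice, because imaging is already counted from it.
- If the full analysis set includes patients who were enrolled but never dosed, a first-dose origin leaves them without a start date. In that case use the enrolment date for both endpoints.
- If survival from diagnosis is still wanted, report it only as a descriptive supplement, with patients entering the risk set (left truncation) at the chosen date.

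The cost is two sentences in the definitions. Sample size and visit schedule do not change, and consent and dosing are already scheduled study events. The one downside for the sponsor is that reported OS becomes slightly less favourable.
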